### Control condition

Participants in the control condition of the RCT will be asked to view a series of text-based slides regarding general drinking behavior. These slides were accessible to be viewed on mobile phones, with content based on information obtained from the Rethinking Drinking website from the National Institute on Alcohol Abuse and Alcoholism (NIAAA).

### Analytic plan

#### Main effects

Main effects of the intervention will be evaluated for pregaming drinking, general drinking (i.e., drinks consumed both during and after pregaming), and alcohol-related consequences in the immediate term and short-term. In the immediate term, we will evaluate whether intervention participants pregame less frequently (i.e., fewer days per week), reach lower BALs on pregaming days, and consume fewer drinks during pregaming from the two weeks prior to the intervention to the two weeks post-intervention than those in the control condition. Estimated BALs will be calculated using Widmark’s formula, which is the standard method for estimating BAL (using sex, weight, amount consumed, time). We will also evaluate whether, compared to control, intervention participants drink fewer days overall (i.e., pregaming days and non-pregaming days), consume fewer drinks over the course of each drinking day, and report fewer consequences on drinking days from the two weeks prior to the intervention to the two weeks post-intervention. In the short term (baseline to six and 14-weeks post-intervention), we will evaluate main effects of the intervention on pregaming frequency (i.e., pregaming days in the past 30 days) and pregaming quantity (i.e., typical amount consumed during pregaming on pregaming days in the past 30 days). We will also evaluate main effects of the intervention on overall drinking days (i.e., pregaming days and non-pregaming days) in the past 30 days, average consumed on a typical drinking day in the past 30 days, and number of alcohol-related consequences experienced in the past 30 days.

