## Methods/Design

### Procedures

For this study, we propose to develop and test a brief mobile (i.e., mobile phone-friendly website) intervention directly targeting pregaming among college students. First, we developed the intervention content and programmed the online intervention. We then beta-tested the developed program with heavy drinking college students who reported pregaming at least once per week on average and gathered feedback regarding feasibility and acceptability of intervention content. Final edits to the brief intervention were made based on these students’ feedback. Next, we will conduct a randomized controlled trial (RCT) of the intervention with approximately 500 college students from one private southern California university, assigning half to intervention and half to control. We will evaluate immediate term (from two weeks pre-intervention to two weeks post-intervention) and short term (from one month pre-intervention to six weeks and 14 weeks post-intervention) drinking during pregaming, overall drinking, and consequences.

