PACE content also focused on goals for the night (i.e., reasons for pregaming) and students learn that they can get what they want out of the night (e.g., feel relaxed, be more social) by drinking moderately or not at all during pregaming. Relatedly, participant’s pregaming-specific expectancies and beliefs that pregaming will make their night better are challenged through a presentation on alcohol placebo studies, where students hear about experiments where college students display the social effects of drinking even without consuming actual alcohol. This is important because students with positive outcome expectancies (e.g., it would be easier to talk to people) are more likely to pregame, and pregaming mediates the relationship between expectancies and hazardous drinking [74]. Participant’s drink refusal skills are reviewed with alternate strategies to use if feeling pressured to drink heavily during pregaming, as greater drink refusal self-efficacy associates with less pregaming [75]. As in a relapse prevention approach, which targets the people, situations, and feelings that may lead one to drink heavily [63], risky situations specific to the students (e.g., when in a large group, when getting ready to meet a potential romantic partner later that night) are reviewed. Protective drinking strategies specific to pregaming [73] are selected by the students and they are asked to try during their next pregaming event strategies they do not normally use.

The intervention concludes with a video summarizing the content and a personalized feedback sheet with resources, that also gets emailed to participants. The personalized feedback sheet contains the information from the intervention in a format viewable at a later time, as well as resources for seeking help on campus and in the community for drinking, sexual violence, and mental health.

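### BAL and the other per-occasion outcomes are compared only on pregaming or drinking days that occur after randomisation, although PACE also aims to reduce those days; per-participant totals should be added

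*Protocol article*

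**What the plan says.** All of this is in the protocol article.

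- **Immediate term (Main effects).** Over the two weeks after the intervention, PACE participants are expected to pregame on fewer days per week, "reach lower BALs on pregaming days, and consume fewer drinks during pregaming". They are also expected to drink on fewer days, "consume fewer drinks over the course of each drinking day, and report fewer consequences on drinking days".
- **Six and 14 weeks (Main effects).** Pregaming quantity is the "typical amount consumed during pregaming on pregaming days in the past 30 days". Overall quantity is the average on a typical drinking day. Pregaming days, drinking days and the number of consequences are 30-day counts.
- **Label (Main effects).** The outcome family is introduced as "general drinking (i.e., drinks consumed both during and after pregaming", but the outcomes listed under it cover days with and without pregaming.
- **Intervention content.** Students are taught that they can get what they want from the night "by drinking moderately or not at all during pregaming", and that peers pregame less often than they think.
- **Daily surveys.** Every survey asks whether the student drank the day before. Pregaming drinks are asked only if the student pregamed, and consequences only if the student drank.
- **Baseline and follow-up surveys.** The 30-day pregaming-quantity item refers to days on which the respondent drank, not days on which they pregamed, and allows an answer of 0.

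**The concern.** BAL on pregaming days, drinks per drinking day and the 30-day typical amounts are defined only when a pregaming or drinking day occurs. Immediate-term drinks during pregaming and consequences on drinking days share this feature if they are read per day. Whether such a day occurs is itself something PACE tries to change. The days, and in part the people, being compared are then selected after randomisation, possibly differently by arm. A student who stops pregaming supplies no post-intervention BAL. A student who gives up only lighter occasions shows a higher average.

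The Abstract's ultimate goal is to affect global drinking and prevent consequences. The direct measure of that is the amount consumed per randomised student. Main effects does not clearly name such a total, for pregaming drinks or for all drinks.

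**Working it through.** The article gives no figure on this point to reproduce. The checks below are illustrations.

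**Inputs from the article:** about 500 students in two equal arms ("approximately 500 college students from one private southern California university, assigning half to intervention and half to control"); pregaming at least once per week at entry (Procedures); three to five drinks per pregaming occasion (Background). **Assumed:** Poisson occurrence of pregaming days, the size of any cut in frequency, the pattern of days removed, and the standard deviations.

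**1. Who has a per-occasion value.** P(no pregaming day) = exp(−expected days).
- One per week, 14 days: control exp(−2) = 13.5%. PACE with a 30% cut: exp(−2 × 0.7) = exp(−1.4) = 24.7%. Of 250 per arm, that is about 34 against 62 students.
- Two per week, 14 days: control exp(−4) = 1.8%. PACE: exp(−2.8) = 6.1%.
- One per week, 30 days: control exp(−30/7) = 1.4%. PACE: exp(−3) = 5.0%.

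**2. Which occasions remain.** Take half of occasions at 3 drinks and half at 5 (mean 4.0). In each case 25% of days are removed.
- Half of the light ones removed: total = 0.25 × 3 + 0.5 × 5 = 3.25 per original occasion, and 3.25/4 − 1 = −18.8%. Per-occasion mean = 3.25/0.75 = 4.33.
- Removed at random: total −25%, mean unchanged at 4.0.
- Half of the heavy ones removed: total = 0.5 × 3 + 0.25 × 5 = 2.75, or −31.3%. Mean = 2.75/0.75 = 3.67.

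**3. Simulation.** 250 per arm, 1.5 pregames per week, mean 4 drinks, between-person SD 1.0, within-person SD 1.5, 14-day post-period comparison, two-sided 5% test, 1,500 repeats. Light means 4 drinks or fewer; heavy means 4 or more. Differences are PACE minus control, and the control total is 12.1 drinks.

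| Days PACE removes | Per-occasion difference | Significant harm / benefit | Difference in 14-day total | Significant benefit on total |
|---|---|---|---|---|
| 15%, all light | +0.15 | 23% / 0.1% | −1.28 | 44% |
| 25%, all light | +0.30 | 62% / 0% | −2.18 | 87% |
| 25%, all from lighter drinkers | +0.08 | 8% / 0.3% | −2.45 | 91% |
| 25%, at random | 0.00 | 3% / 3% | −3.03 | 99% |
| 25%, all heavy | −0.29 | 0% / 62% | −3.86 | 100% |
| 25% light, remaining occasions cut by 0.5 drink | −0.20 | 0.1% / 33% | −3.29 | 100% |
| 25% light, remaining occasions cut by 1 drink | −0.70 | 0% / 99.8% | −4.43 | 100% |

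The total has the right sign in every row. The per-occasion mean does not.

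**The case against.** - **Much of the randomised comparison is intact.** A reader might infer that it is lost for the trial as a whole. The article does not support that: pregaming days, drinking days and the 30-day consequence count are defined for everyone. A loss of light days would show as fewer pregaming days beside a higher mean, not as harm alone. This stands.
- **Apparent harm is not the expected result.** It requires PACE to remove light occasions preferentially, and nothing in the article says that it will. Random removal gives no per-occasion difference, removal of heavy days gives an apparent benefit, and a one-drink cut outweighs the selection. This stands. What remains is that the direction cannot be known in advance and that random removal hides a real reduction.
- **Some wording is open.** Fewer drinks during pregaming, and fewer consequences on drinking days, can both be read as totals. The 30-day pregaming item lets a drinker who has stopped pregaming answer 0, so selection there may be weaker than Main effects implies. This stands, and it is why those outcomes are included only on the per-day reading.
- **Few students would lack a drinking day.** Background puts around one-third or more of drinking days as pregaming days. Two pregaming days then imply about 6 drinking days at one-third, exp(−6) = 0.25% with none, or 4 at one-half, exp(−4) = 1.8%. This stands for drop-out from the comparison. It does not address the changed mix of days among those who still drink.
- **Per-occasion intensity is a stated target.** Limiting the amount drunk while pregaming is an aim of PACE, so there is no need to demote BAL or quantity. This stands.

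The handling of zeros within a model may be left to an analysis plan. The point here is the outcome definitions that the article itself fixes.

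**Conclusion.** The concern holds for BAL on pregaming days, drinks per drinking day and the 6- and 14-week typical amounts. On the per-day reading it also holds for immediate-term drinks during pregaming and consequences on drinking days. Taken alone, these comparisons cannot show whether PACE reduced drinking, because selection can raise, hide or flatter the per-occasion mean while total consumption falls.

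The size depends on assumptions that the article cannot settle. The gap of 13.5% against 24.7% without a pregaming day is the figure at the entry floor and shrinks quickly as students pregame more often. The shifts of about 0.3 drink either way in the simulation come from assumed removal of 25% of days by occasion size. The mechanism itself needs only that PACE changes the number of pregaming or drinking days, which the article sets out to test.

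**What to change.** 1. Add three 14-day totals from the daily surveys for every randomised participant: pregaming drinks, drinks on all days, and consequences. Reported days without pregaming or drinking count as 0. Missed surveys are treated as missing, not as 0. Base the conclusion about overall reduction on these totals.
2. Keep BAL and the per-occasion quantities. Present them beside the frequency result and do not read them as stand-alone evidence of benefit or harm.
3. At 6 and 14 weeks, derive total drinks as drinking days × average drinks per drinking day, 0 if none. Before deriving a pregaming total in the same way, reconcile the survey item (days on which the student drank) with Main effects (pregaming days). If respondents average over all drinking days, multiplying by pregaming days would understate the total.
4. Define general drinking as all drinks on all days.

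The cost is wording and a few extra derived outcomes; the daily surveys already collect what the 14-day totals need.

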#### Moderation

We will evaluate moderation by augmenting main effect models with interactions between four moderators of interest and the intervention. Significant interactions with sex, for example, will be indicative of an effect modification where the impact of the intervention can be different for men and women even if both groups realize a significant impact of the intervention. We will test four moderators of intervention efficacy: sex, age, baseline hazardous drinking scores on the Alcohol Use Disorders Identification Test (AUDIT) [76], and baseline motivation to change drinking. These moderators were selected based on the pregaming literature and to help determine the feasibility of this approach in spite of variations in behavior during the event. First, female students have been found to be at particular risk from pregaming, including higher pregaming BALs and subsequent hospitalizations [40, 49, 52, 77–79]. Thus, we hypothesize that women will benefit most from the intervention. Second, though there are few differences observed in pregaming frequency between students under 21 and 21 or older, students under age 21 have reported reaching higher BALs during pregaming than of-age students and are hypothesized to benefit most [36, 80]. Third, baseline levels of hazardous drinking will also be explored as a moderator, as heavier global drinkers drink more during pregaming [41, 81–83]. We hypothesize baseline heavier drinkers will benefit most.

#### Outcome measures

On all surveys, we will define pregaming behavior for participants as the following: “When we ask you about pregaming (a.k.a., prepartying), we are talking about the consumption of alcohol prior to attending an event or activity. For example, drinking before going to a party, bar, concert, sporting event, date, meeting, or any other event or activity at which more alcohol may or may not be consumed. This can be an event that has a large number of people or very few people.” Participants will also be provided with a graphic depicting standard drinks (i.e., 12 oz of beer with 5% alcohol/volume, 8–9 oz of craft beer with approximately 7% alcohol/volume, 4–5 oz of wine with approximately 13% alcohol/volume, 12 oz of hard seltzer with 5% alcohol/volume, 1.5 oz of 80 proof liquor with 40% alcohol/volume in either a shot glass or in a mixed drink).

#### Baseline and follow-up surveys

On the screening questionnaire, participants will be asked, “During the past 30 days, how often did you engage in pregaming,” with response options of never, just once, a couple of times, about once per week, a couple of times per week, and daily or almost daily. Those endorsing about once per week or more will screen into the study and complete the baseline survey. Overall drinking frequency will be assessed with an item asking, “During the past 30 days, how many days did you have at least one drink of any alcoholic beverage, such as beer, wine, hard seltzer, mixed drinks, or shots of liquor,” with response options from 0 to 30 days. To assess overall drinking quantity, participants will then be asked to consider their typical drinking behavior over the past 30 days with, “During the past 30 days, on the days when you drank, about how many drinks did you drink on average,” with response options from 0 to 30 drinks. Pregaming frequency will then be asked with the item, “During the past 30 days, how many days did you engage in pregaming,” with response options from 0 to 30 days. Pregaming quantity will be assessed with an item asking, “During the past 30 days, on the days when you drank, about how many drinks did you drink during pregaming,” with response options from 0 to 30 drinks. Alcohol consequences will be assessed with the Brief Young Adult Alcohol Consequences Questionnaire (B-YAACQ) [84, 85], where participants will indicate which (yes/no) of 24 alcohol-related consequences have happened to them in the past 30 days (e.g., I drove a car when I knew I had too much to drink to drive safely, I did not remember large stretches of time while drinking heavily). Participants will indicate race/ethnicity and class year (for descriptive purposes), age and biological sex (for moderation analyses), weight (for calculating estimated BAL), complete the 10-item AUDIT [76] (for moderation analyses), and indicate how motivated they are to drink less using a change ruler (scale from 0–10) modified from other work [86, 87] (for moderation analyses). Follow-up surveys will also ask intervention and control participants how long they spent viewing the content and whether they returned to review the content after initial viewing. Back-end data connected to PIN codes can also be used to determine whether participants finished viewing the intervention or control content or only completed a portion of either.

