Among U.S. students, around one-third or more of all drinking days involve pregaming [35, 40, 47, 48], with students typically consuming between three to five drinks within just one to two hours [35, 49]. Such quick-paced drinking can lead to high blood alcohol levels (BALs), which are reached even before students leave for their intended destination, at which point they often go on to drink more. To wit, most pregaming events involve further drinking once students reach their intended destination [49, 50], which typically results in a total drink count for the night indicative of high intensity drinking (i.e., 10 or more drinks) [51]. High BALs can lead to negative consequences on a night out, and severe alcohol-related consequences have been linked to pregaming drinking, including hospitalizations, regretted sex, driving after drinking, blacking out, and passing out [35, 40, 43, 49, 52–55]. Further, students drink more on pregaming nights than on non-pregaming nights [35, 40, 43, 49, 54, 55], and longitudinal research shows that pregaming frequency predicts heavy drinking behavior and alcohol-related consequences even up to one year later [42], suggesting long term impacts on risky alcohol use trajectories.

Given the risks associated with pregaming, it would be important for interventions that target drinking globally to also affect changes in pregaming behavior specifically. Yet, interventions that target general drinking patterns do not show effects on pregaming behavior. For example, one published study evaluated pregaming outcomes after a global, brief, group intervention with mandated students and failed to find significant reductions in pregaming post-intervention, even if pregaming was mentioned (albeit infrequently) by students in the discussion portions of the intervention [56]. Another study found that a general alcohol-reduction intervention for student-athletes did not reduce athletes’ pregaming behavior one- and four-months post-intervention [57]. Thus, approaches specifically targeting pregaming may be necessary for reductions to occur in pregaming-specific heavy drinking. Such an approach can selectively target the specific behavior known to lead to subsequent consequences and heavy drinking both on the pregaming day and more generally.

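### The six- and 14-week pregaming quantity outcome is defined per pregaming day, but the survey item that measures it refers to all drinking days

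*Protocol article*

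**What the plan says.** The Main effects section of the protocol article lists five short-term outcomes at six and 14 weeks. One is pregaming quantity, defined as "typical amount consumed during pregaming on pregaming days in the past 30 days". Two others are "pregaming frequency (i.e., pregaming days in the past 30 days" and "overall drinking days (i.e., pregaming days and non-pregaming days". The remaining two are the average amount on a typical drinking day and the number of consequences.

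The Baseline and follow-up surveys section gives the items in full and in order: overall drinking frequency, overall drinking quantity, pregaming frequency, pregaming quantity. The overall quantity item asks, for the past 30 days, "on the days when you drank, about how many drinks did you drink on average". The pregaming quantity item asks, for the same period, "on the days when you drank, about how many drinks did you drink during pregaming".

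The Daily surveys section works differently: the number of pregaming drinks is asked only when the participant reports having pregamed the day before.

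**The concern.** The outcome is conditioned on pregaming days and the item on drinking days. The article itself counts days without pregaming as drinking days. The opening of the item is also shared with the overall quantity item two questions earlier, where it can only mean all drinking days. A student who carries that meaning forward averages in days with no pregaming drinks.

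The stake is what the six- and 14-week result can be taken to mean. Limiting the amount drunk while pregaming is the stated purpose of the intervention, and the daily surveys end two weeks after it, so this item is the only described measure of drinks per pregaming day at the later times. Answered literally, it also carries pregaming frequency and overall drinking days, which are separate outcomes that the intervention is meant to change.

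**Working it through.** The plan states no figure derived from this item, so there is nothing to reproduce. The check sets the definition against the item and works out what a literal answer would return.

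**Notation**
- Q = drinks per pregaming day (the defined outcome).
- P = pregaming days in the past 30 days.
- D = all drinking days in the past 30 days.
- Literal answer = Q × P / D.

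**Inputs from the Background section**
- Q: "students typically consuming between three to five drinks within just one to two hours", so 3 to 5.
- P/D: "around one-third or more of all drinking days involve pregaming", so one-third is a floor, and it describes US students generally. Eligible students here pregame at least once a week, so their share may be higher. The range one-third to 1 is therefore shown.

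**Literal answer against the defined value**

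| P/D | Q = 3 | Q = 5 |
|---|---|---|
| 1/3 | 3 × 1/3 = 1.0 | 5 × 1/3 = 1.67 |
| 1/2 | 1.5 | 2.5 |
| 3/4 | 2.25 | 3.75 |
| 1 | 3.0 | 5.0 |

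The item returns the defined outcome only when every drinking day is a pregaming day.

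**What moves the literal answer when quantity does not change.** Q is fixed at 4, so the true effect on quantity is zero. The day counts are assumptions chosen for illustration.
- P falls from 4 to 3, D stays at 12: 4 × 4/12 = 1.33 becomes 4 × 3/12 = 1.00, a change of −25%.
- P falls from 4 to 3 and D from 12 to 11: 1.33 becomes 4 × 3/11 = 1.09, or −18%.
- P falls from 6 to 5 and D from 8 to 7: 4 × 6/8 = 3.00 becomes 4 × 5/7 = 2.86, or −5%.
- P stays at 4, D falls from 12 to 10: 1.33 becomes 4 × 4/10 = 1.60, or +20%.

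The movement can go either way. Its size depends on the starting share and on whether a dropped pregame also removes a drinking day.

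**Mixed readings.** If a fraction λ of students answer literally, and the reading is unrelated to Q and P/D, the mean is Q × (λ × P/D + 1 − λ). Taking λ = 1/2 purely as an example, the first case above goes from 4 × (0.5 × 1/3 + 0.5) = 2.67 to 4 × (0.5 × 1/4 + 0.5) = 2.50, about −6% rather than −25%. The documents give no value for λ.

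**The case against.** A reader might infer that the outcome is certainly measured on the wrong denominator, and that an effect on frequency alone will show up as a fall in quantity. The documents do not support that. The pregaming item drops the request for an average that the overall quantity item contains, and it comes directly after the question on the number of pregaming days. Every survey also carries a definition of pregaming. Many students may therefore answer per pregaming occasion, which is the intended quantity. This stands, and it makes the bias conditional.

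A reader might also take the one-third share as the figure for this trial. It is a lower bound for students in general, whereas this sample is selected for weekly pregaming. At a share of three-quarters the gap is much smaller.

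The reach is limited. Four of the five short-term outcomes and the immediate-term quantity outcome are untouched. Both arms receive the same item, so if the intervention changed no drinking behaviour and both arms read the item alike, the wording would create no difference between them. One could speculate that the intervention, which itself asks about the amount per pregaming occasion, shifts how its recipients read the item at follow-up. Nothing in the article shows that it does.

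Finally, the article may have misprinted the item; the fielded questionnaire is not shown. None of this removes the mismatch. The item is quoted in full and the definition is explicit, so this is not detail lost in condensing.

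**Conclusion.** The inconsistency is real and confined to one short-term outcome, at baseline and at six and 14 weeks. Read literally, the item returns Q × P / D instead of Q. For 3 to 5 drinks per pregame, that is between 1.0 to 1.67 (share one-third) and 3 to 5 (share 1). Under that reading, a change in pregaming frequency or in other drinking days may register as a change in quantity. With mixed readings the variable is a noisy blend, and rescaling by D/P cannot recover Q because it is not known who answered which way.

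The mismatch rests on the text alone. The size rests on the Background figures, on assumed day counts, and on an unknown share of literal answers, so the numbers show a range and are not an estimate of bias in this trial. As the text stands, the six- and 14-week result cannot safely carry the meaning that the Main effects section gives it. The trial's other comparisons are not in question.

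**What to change.** Check the fielded questionnaire first. What follows depends on what it shows.

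- **The article misprinted the item.** Correct the text. Nothing else changes.
- **The wording is as printed and no wave has been fielded.** Change the reference days to those on which the student pregamed, at baseline and both follow-ups. State how participants who report no pregaming days enter the comparison: per-pregame quantity has no value for them, and restricting to those who still pregame selects on something that happens after randomisation. The cost is one edited item, a minor notification to the ethics board and a sentence in the analysis plan, with no added participant burden.
- **Data have already been collected with this wording.** This is possible, since the Limitations section says recruitment began in fall 2021. Keep the item unchanged, because a switch partway would break comparability with baseline. Redefine and label the outcome to match the item, without describing it as a per-pregaming-day amount, and interpret it together with pregaming frequency and overall drinking days. Use the daily data for drinks per pregaming day, noting that they cover only the two weeks after the intervention and cannot stand in for the six- and 14-week results. The cost is a change of definition and label, and a narrower claim.
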